## Abstract

**Background:**

Stroke is a debilitating disease affecting millions of people worldwide. Despite the survival rate has significantly increased over the years, many stroke survivors are left with severe impairments impacting their quality of life. Rehabilitation programs have proved to be successful in improving the recovery process. However, a reliable model of sensorimotor recovery and a clear identification of predictive markers of rehabilitation-induced recovery are still needed. This article introduces the cross-modality protocols designed to investigate the rehabilitation treatment’s effect in a group of stroke survivors.

**Methods/design:**

A total of 75 stroke patients, admitted at the IRCCS San Camillo rehabilitation Hospital in Venice (Italy), will be included in this study. Here, we describe the rehabilitation programs, clinical, neuropsychological, and physiological/imaging [including electroencephalography (EEG), transcranial magnetic stimulation (TMS), and magnetic resonance imaging (MRI) techniques] protocols set up for this study. Blood collection for the characterization of predictive biological biomarkers will also be taken. Measures derived from data acquired will be used as candidate predictors of motor recovery.

**Discussion/summary:**

The integration of cutting-edge physiological and imaging techniques, with clinical and cognitive assessment, dose of rehabilitation and biological variables will provide a unique opportunity to define a predictive model of recovery in stroke patients. Taken together, the data acquired in this project will help to define a model of rehabilitation induced sensorimotor recovery, with the final aim of developing personalized treatments promoting the greatest chance of recovery of the compromised functions.

## 1. Introduction

Stroke is a cerebrovascular disease representing the third cause of death in high socio-demographic countries (Institute for Health Metrics and Evaluation [IHME], 2018). Improvements in prevention and treatment of the acute stage have significantly increased the survival rate. However, stroke remains a leading cause of severe long-term motor disability, affecting the quality of life of stroke survivors, limiting their return to a normal life, and representing a burden for their families. Worldwide there are over 33 million stroke survivors most of whom suffer from long-term disability (Feigin and Krishnamurthi, 2010).

Upper limb (UL) impairment represents the most impacting long-term disability caused by stroke. Among stroke survivors, motor impairment can be related to different aspects of movement, such as motor planning, learning, and control (Pollock et al., 2014). The aim of rehabilitation-mediated recovery is twofold: (i) minimize sequelae and (ii) improve the recovery of the affected limb(s).

Despite important advances in the medical and physical rehabilitation fields, neurological rehabilitation still lacks a reliable physiological model of UL sensorimotor recovery after stroke. For example, the magnitude of the motor recovery, occurring after rehabilitation treatment, that can be effectively attributed to the rehabilitation process itself is still largely unclear. Moreover, a precise identification and characterization of the key markers to be used as predictive factors of rehabilitation-induced recovery is needed (Hayward et al., 2017).

To date, both in clinical trials and current clinical practice, many treatment methods and assessment tools are available for quantification of the final outcome. Alongside the traditional therapeutic approaches (generally referred as “Conventional Therapy,” CT) based on neurodevelopmental principles, the so-called “innovative approaches” (e.g., robotics and virtual reality – VR) emerged recently providing an augmented environment with reinforced feedback to the patient. These technology-based methods have become popular, although current evidence on their efficacy is still under investigation (Feigin and Krishnamurthi, 2010; Bernhardt et al., 2016).

Evidence suggests that spontaneous recovery expresses its maximum effect from 3 to 6 months (Bernhardt et al., 2017), nevertheless recent results demonstrated that rehabilitation interventions can promote clinically significant improvements of motor outcomes even after this sensitive window, especially if high dose of therapy is provided (Daly et al., 2019; Ward et al., 2019). Indeed, motor improvements in UL recovery were found to be achieved after 90–300 h of rehabilitation, even in the chronic phase (Daly et al., 2019; Ward et al., 2019). Moreover, data available in the literature also emphasize the importance of the so-called “active ingredients” of rehabilitation (i.e., the specific elements which are assumed to be responsible for the treatment effect), but which are often not defined, classified, or measured (Ward et al., 2019).

During motor performance, there is an integration between motor and cognitive components (Barrett and Muzaffar, 2014; D’Imperio et al., 2021). For example, the control of sensorimotor aspects of motor actions requires attentional and cognitive demands, especially when performing complex movements. Consequently, cognitive abilities, such as attention, may play a key role, particularly in individuals recovering from stroke, as suggested by several studies (McDowd et al., 2003; Krakauer, 2006; Shafizadeh et al., 2017; VanGilder et al., 2020). This indicates that the identification of cognitive skills capable of guiding and predicting motor recovery could help in “*a priori*” patients stratification based on different recovery potentials.

Alongside motor recovery, prediction of the optimal level of functional improvement to be expected, is also a critical aspect in the stroke rehabilitation field. Indeed, prediction may be a useful guidance for setting rehabilitation goals and monitoring patient’s achievements over time (Piscitelli et al., 2018). Up to date, literature has mainly focused on prognostic factors (i.e., considering spontaneous recovery) rather than predictive ones (i.e., considering response to a rehabilitative intervention) (Clark, 2008). Coupar et al. in a systematic review examined potential factors for predicting UL recovery, such as: (i) preserved conduction and anatomical integrity of the cortico-spinal tract (CST) confirmed by motor evoked potentials (MEPs), and fractional anisotropy (FA), respectively; (ii) preserved sensation function; (iii) strong Shoulder Abduction and Finger Extension (SAFE) (Coupar et al., 2012; Stinear et al., 2017b). However, these studies did not take into account whether patients received rehabilitation or the dosage and modalities used, therefore, the impact of therapy and/or dosage on the accuracy of predictions has not yet been evaluated (Coupar et al., 2012; Stinear et al., 2017b). One study suggested that the best predictors of response to robotic treatment were preserved CST integrity, great ipsilesional motor cortex activation, and great interhemispheric connectivity, although the dosage used was still relatively low and not investigated as a factor potentially influencing the recovery prediction (Burke Quinlan et al., 2015). Likewise, improvement of motor functions after stroke can be associated with some changes in brain activity and connectivity as measured with electroencephalography (EEG): on inter-regional synchronization of neural oscillations (Nicolo et al., 2015; Romeo et al., 2021), on the evoked responses as measured in an oddball task (Naatanen et al., 2012), or in the brain oscillations evoked during gamma entrainment (Pellegrino et al., 2019). Some recent results also suggest that the aperiodic component of the power spectrum can have an important prognostic role in brain damaged patients (Maschke et al., 2023).

With regards to recovery prediction, data from the literature suggest that specific algorithms can be used to provide an accurate prediction of UL functional recovery. These algorithms are mostly based on clinical, imaging (magnetic resonance imaging – MRI) and neurophysiological (MEPs, collected with transcranial magnetic stimulation – TMS) measures. However, the validity of such models has been investigated only with assessments performed within a time window from 2 to 11 days (i.e., 2, 3, 5, 9, and 11 days) and UL prediction recovery at 3 months (Stinear, 2017). Moreover, factors such as: (i) variability in time of patient transfer to rehabilitation facilities, (ii) absence or delay in the acquisition of timely specific information (i.e., MEPs, FA, and National Institute of Health Stroke Scale – NIHSS), and (iii) different phases of recovery (i.e., subacute and chronic) when patients join the rehabilitation care, represent some of the most common confounders that can severely affect the predictive accuracy of the algorithms (Smania et al., 2009; Stinear, 2010, 2017; Stinear et al., 2012, 2017a). If only clinical outcome measures are available, predicting the effect of true recovery due to “treatment” over time is virtually impossible. Indeed, standalone clinical measures do not allow the thorough interpretation of the mechanisms underlying UL functional recovery (Stinear et al., 2007). For these reasons, imaging and physiological techniques, such as functional magnetic resonance imaging (fMRI) and TMS, have been previously used to accrue information on motor-related brain regions functionality following stroke recovery (Allman et al., 2016; Smith and Stinear, 2016). Similarly, diffusion tensor imaging (DTI) technique can be used to determine the anatomo-histological integrity of motor-related white matter (WM) pathways (Stinear et al., 2007). Recent preliminary studies have also suggested that measuring plasma levels of specific miRNAs (small RNA molecules that act as regulators of cell development, proliferation, cycling, and differentiation), and determining the specific genetic profile of stroke patients could provide useful biologically derived predictive markers of functional recovery (Chang et al., 2016; Edwardson et al., 2018; Dimyan et al., 2022).

Here, we report the protocol of the study “NeuroPro” (Investigation of NEUROphysiological substrates of UL sensorimotor impairment after stroke and PROgnosis of rehabilitation-induced recovery of motor function: longitudinal study), which is a longitudinal study employing a multi-dimensional and multi-modal approach to evaluate motor function and predict recovery in stroke inpatients in a clinical setting. We will combine clinical, biological, neurophysiological/imaging, neuropsychological, and rehabilitation measures with the final aim of developing a multidimensional predictive model of motor recovery after stroke. Whereas clinical, neuropsychological, and rehabilitation measures are usually acquired in ecological clinical settings, the possibility of performing this study in a rehabilitation research center, with both clinical and research compounds in the same institute, will allow a detailed characterization of participants (e.g., clinical profiling, operationalization of pharmacological treatment, and individual frailty levels). Moreover, the access to neurophysiological/imaging and biological facilities, will grant us the possibility to acquire a set of specific measures to develop a comprehensive and sensitive model of motor recovery, after rehabilitation treatments in stroke survivors.

## 2. Objectives

The overarching objective of this project is to identify a set of variables, from a wide range of assessment modalities, which can reliably predict UL motor recovery after stroke, in patients undergoing rehabilitation in a clinical setting. This will help us to: (i) examine clinical features (e.g., behavioral, physiological, neural, and biological) associated with rehabilitation-induced recovery for identifying best responders to UL behavioral intervention, for rehabilitation after stroke, (ii) understand which modalities are the most suitable for a specific patient and the respective optimal dosage, and (iii) establish most effective times from onset of the acute event for modalities referral.

The richness of data acquired will also contribute to add new evidence on the predictive value of some emerging motor features (e.g., SAFE), biological markers (e.g., miR-941 levels), or physiological measures (e.g., EEG aperiodic parameters), described in greater detail in section “3. Materials and methods,” with the potential of being translated into current clinical practice.

## 3. Materials and methods

For a full and comprehensive reporting of the present study, the *transparent reporting of a multivariable prediction model for individual prognosis or diagnosis* (TRIPOD) will be used (Collins et al., 2015).

### 3.1. Funding, ethics, and data access

The study *NeuroPro* is partially funded by the RF-2018-12366899 “Brain connectivity measured with high-density electroencephalography: a novel neurodiagnostic tool for stroke” and GR-2018-12366092 “Assessment and treatment of communicative pragmatic abilities in neurological and psychiatric disorders: feasibility and clinical efficacy” grants by the Italian Ministry of Health.

Ethical approval was granted by the “Comitato etico per la Sperimentazione Clinica (CESC) della Provincia di Venezia e IRCCS San Camillo” (Prot. 1375/IRCCS San Camillo). The protocol has been registered on ClinicalTrials.gov (NCT05423119). Data collection for this study started in August 2021 and will be completed by February 2024. The study is carried out according to the Declaration of Helsinki. Written informed consent is obtained from all patients. Data are anonymized before being processed and stored on password protected computers or in protected areas within the IRCCS San Camillo Hospital infrastructures. All personal information (i.e., names and addresses) is stored separately in locked-filing cabinets. Only authorized personnel have access to patients’ data.

Data can be accessed upon request to the IRCCS San Camillo Hospital according to GDPR and Italian regulations for the privacy of biomedical data. A submission to the local ethical committee and informed consent from the participants may be required.

### 3.2. Participants’ recruitment and study design

#### 3.2.1. Participants

Study participants are recruited among stroke survivors admitted to a period of intensive neurorehabilitation treatment at the IRCCS San Camillo Hospital in Venice, Italy.

Inclusion criteria are: (1) age ≥18 years old; and (2) first ever cortical-subcortical, supratentorial ischemic or hemorrhagic, unilateral stroke, based on medical records.

Exclusion criteria are: (1) bilateral or pure cerebellar lesion; (2) presence of non-stabilized fractures; (3) diagnosis of other neurological and/or psychiatric disorder; (4) unstable medical condition (e.g., heart failure, untreated seizures, and psychiatric comorbidities); (5) any other relevant UL musculoskeletal impairment both before and after stroke, hampering assessment; and (6) inability to provide informed consent. Specific inclusion criteria for imaging analyses are (1) distinguishable lesion in FLAIR and (2) unilateral hemisphere lesion, while exclusion criteria are (1) bilateral lesion and (2) non-distinguishable lesion in FLAIR.

Specific exclusion criteria related to the instrumental technology (i.e., EEG, MRI, and TMS) employed in this project will be detailed in each specific section.

#### 3.2.2. Sample size calculation

The sample size was calculated with regard to the main motor outcome assessing UL function (Fugl-Meyer Assessment for Upper Extremity – FMA-UE). From published data on the same cohort study design of stroke survivors admitted at the IRCCS San Camillo Hospital (Salvalaggio et al., 2023), and undergoing the same rehabilitative treatments described in this protocol, is expected that UL function improves with moderate standardized effect (Cohen’s *d* = 0.45), according to FMA-UE. Assuming an equivalent effect size *f* = 0.225, for repeated measures, within factors multivariate analysis of variance (MANOVA) design (Chen and Chen, 2010), in one group with two measurements correlating 0.5, given α = 0.05 and 1-β = 0.90, a total recruitment of 54 consecutive subjects would be needed. Considering a drop-out rate of 40%, a final number of 75 patients will be considered sufficient to conclude the study.

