### 3.5. Statistical modeling

Statistical methods will be based on the intention-to-treat principle (McCoy, 2017). Given the heterogeneity of the measures collected, data will be normalized before being analyzed and in case of high percentages of missing data, they will be subjected to multivariate imputation (Sterne et al., 2009). The statistical analysis will be as follow:

–Descriptive statistics (median, interquartile range, mean, standard deviation, and absolute and percentage frequencies) will be applied to describe the sample characteristics and data.–Data distribution, assessed with the Shapiro–Wilk test, and appropriate correlation tests (i.e., Spearman’s rho, Pearson’s *r*, Cramér’s V, or point-biserial correlation coefficient) will be performed to study the presence of associations between the variables (collinearity).–Data grouping. Patients will be divided in two categories (i.e., *Responders* and *Non-Responders*) according to responsiveness to therapy, defined as an improvement of 5 points relative to the minimally clinically important difference (MCID) of the primary outcome measure (i.e., FMA-UE) (Page et al., 2012). To assess whether there is a statistically significant difference in the dose of therapy between the Responder and Non-Responder patient groups, Student’s *t*-test for unpaired data or Mann–Whitney test for each clinical variable will be performed, depending on distribution properties, as already proposed in previous studies (Salvalaggio et al., 2023). Then, with the aim to identifying the best set of variables (regressors) that can predict UL motor recovery in patients, appropriate regression models will be estimated. This step will be preceded by the evaluation of the requirements of the chosen model and by considering possible adjustments for mediating, moderating, and confounding factors. Prior to model fitting, preliminary diagnostic check will be made [i.e., variance inflation factor (VIF) for the study of collinearity independence among predictors]. Selection of the best set of regressors will be made taking into account appropriate indices. A diagnostic analysis (goodness-of-fit) of the model will be performed on the model to verify its assumptions and the fit to the available data. The statistical significance level will be set at *p* < 0.05, and all statistical analyses will be performed using the latest version of R software (R Core Team, 2022).

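### The 54 patients and 90% power belong to a pre-post FMA-UE test that section 3.5 does not list, so they do not cover the Responder comparisons or the prediction model

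*Protocol article*

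**What the plan says.** Section 3.2.2 states the basis of the sample size: "The sample size was calculated with regard to the main motor outcome assessing UL function", namely FMA-UE. The assumed effect is a within-cohort improvement: "is expected that UL function improves with moderate standardized effect (Cohen’s *d* = 0.45), according to FMA-UE". This is carried into the calculation as follows: "Assuming an equivalent effect size *f* = 0.225, for repeated measures, within factors multivariate analysis of variance (MANOVA) design", "in one group with two measurements correlating 0.5", "given α = 0.05 and 1-β = 0.90". The result is "a total recruitment of 54 consecutive subjects would be needed", which a 40% drop-out allowance raises to 75, the number the section regards as enough to complete the study.

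Section 2 gives the overarching objective as to "identify a set of variables, from a wide range of assessment modalities, which can reliably predict UL motor recovery after stroke". Section 3 adopts TRIPOD, a reporting standard for prediction models.

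Section 3.5 sets out the analyses: descriptive statistics, distribution and correlation checks, a split into Responders and Non-Responders by a 5-point FMA-UE improvement, an unpaired t-test or Mann-Whitney test "To assess whether there is a statistically significant difference in the dose of therapy between the Responder and Non-Responder patient groups", and regression models with selection of regressors, VIF and goodness-of-fit checks.

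**The concern.** The test that was sized and the analyses that are listed are different things. The sized test asks whether mean FMA-UE changes over the hospital stay in one uncontrolled cohort. A positive answer would identify no predictor of recovery. The listed analyses compare two subgroups of that cohort, or fit a multivariable model to it, and section 3.2.2 contains nothing that sizes either one: no responder share, between-group difference, number of predictors, expected R² or precision target.

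Two things are at stake. First, the article offers one power figure, and it does not apply to the questions the study is designed to answer. Second, nothing in the sizing limits how many candidate predictors the model may screen. Sections 3.2.4 to 3.2.9 and 3.4 supply a long list of them: motor scales, drug classes, dose codings, neuropsychological tests, miR-941, and EEG, TMS and MRI measures including connectivity matrices.

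**Working it through.** **1. The plan's own figure.** Inputs from section 3.2.2: f = 0.225, m = 2 measurements, correlation ρ = 0.5, α = 0.05, target power 0.90. For a one-group within-factor MANOVA the noncentrality is λ = N·f²·m/(1−ρ), with 1 and N−1 degrees of freedom. With these inputs λ = N × 0.050625 × 2/0.5 = 0.2025·N, which equals N × 0.45². The test is therefore a two-sided paired t-test with a standardized change of 0.45.

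- N = 53: power 0.895.
- N = 54: λ = 10.94, power 0.901. This is the smallest N reaching 0.90, so 54 reproduces.
- N = 45: λ = 9.11, power 0.839. This is the number left if 75 are enrolled and 40% are lost (75 × 0.60 = 45).

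The 90% thus belongs to 54 completers. At the plan's own drop-out rate, 75 enrolled give about 84% even for the sized test. (Keeping 54 after 40% loss would take 54/0.60 = 90; that is a separate point.)

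**2. Is the sized test among the listed analyses?** Section 3.5 introduces its contents as the statistical analysis and goes through them in order. No MANOVA, repeated-measures, paired or other T0-T1 test of FMA-UE appears. FMA-UE change enters only as the criterion for the Responder split and as the recovery to be predicted.

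**3. Unpaired comparison.** The article gives no responder share, so a range is assumed. For a two-sided unpaired t-test at α = 0.05, the noncentrality is d·√(n₁n₂/(n₁+n₂)), with n₁+n₂−2 degrees of freedom. Solving for d at 80% power:

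| Completers | 50:50 | 30:70 | 20:80 |
|---|---|---|---|
| 54 | 0.78 | 0.85 | 0.97 |
| 45 | 0.85 | 0.92 | 1.07 |

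Group sizes are 27/27, 16/38 and 11/43 for 54 completers, and 22/23, 14/31 and 9/36 for 45.

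**4. Prediction model.** Assume a linear model, expected shrinkage S of at least 0.9, and R² of 0.3 to 0.5; none of these is in the article.

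- Strict criterion: P = N·(S−1)·ln(1−R²/S). At N = 54, P = 54 × (−0.1) × ln(1−0.3/0.9) = 2.2 for R² = 0.3, and 4.4 for R² = 0.5. At N = 45, P = 1.8 and 3.6.
- Lenient criterion: S = 1 + (P−2)/(N·ln(1−R²app)), where R²app is the apparent R² corresponding to the assumed adjusted R². The largest P with S ≥ 0.9 at N = 54 is 4 (S = 0.915) for R² = 0.3 and 6 (S = 0.909) for R² = 0.5. At N = 45 it is 4 and 5.

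These counts refer to candidate parameters, before selection.

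**The case against.** The strongest reply is that only a condensed article is at hand. A full protocol or analysis plan may contain the pre-post test. That stands: a reader might infer that the sized test is never performed, but the article shows only that section 3.5 does not list it. The reply does not rescue the power statement. Adding the test elsewhere would still leave the 90% silent on the prediction objective.

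A second reply is that section 3.2.2 is open about what it sizes, and that FMA-UE change is the quantity on which Responders are defined and recovery is judged. Both are true. But sizing a mean change in the outcome is not sizing the identification of its predictors.

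A reader might also put d = 0.45 into the unpaired comparison, obtain about 37% power with 54 completers in equal groups, and set that against 90%. The documents do not support this. The 0.45 is a pre-post improvement in FMA-UE, whereas the Responder comparison concerns dose of therapy, and no effect size is given for dose. Only the detectable difference can be stated, and only as a range, because the 50:50 split is the most favourable case and is not documented.

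Finally, a single parameter cap would claim too much. It depends on the assumed R², on the shrinkage criterion and on a linear model. Section 3.5 leaves the type of regression open, and the binary Responder split could lead to a logistic model.

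**Conclusion.** The concern holds in this form: 54 patients and 90% power apply to the mean T0-T1 change in FMA-UE, a test that section 3.5 does not list and that does not address the section 2 objective. The Responder/Non-Responder comparisons and the regression model have no stated power or size justification. This mismatch follows from the text alone and needs no assumption.

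Its size does rest on assumptions. At 80% power the unpaired comparison detects only large differences, from 0.78 (54 completers, equal groups) to 1.07 (45 completers, 20:80). The model supports a handful of candidate parameters: about 2 to 4 on the strict criterion and at most 4 to 6 on the lenient one, for a linear model with R² of 0.3 to 0.5. The documents do not show that the arithmetic behind 54 is wrong (it is right), nor that the pre-post test will not be done.

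**What to change.** Four changes of wording, with no change in enrolment:

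1. In section 3.2.2, state that the 90% power applies only to the mean pre-post FMA-UE change with 54 completers, and that it is about 84% if 75 are enrolled and 40% are lost. Either list that test in section 3.5 or say that it serves only for sizing.
2. Give what the available number supports for the listed comparisons, as a range with its assumptions: a detectable standardized difference at 80% power of about 0.78 to 0.97 with 54 completers and 0.85 to 1.07 with 45, for splits from 50:50 to 20:80.
3. Limit the candidate parameters of the prediction model in advance to a small number, and state the criterion, the assumed R² and the model type. For a linear model this means about 2 to 4 (strict), or at most 4 to 6 (lenient). Recalculate if a logistic model is used.
4. Do not describe the Responder comparisons as covered by the 90% power.

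The cost is that the stated figures become less favourable and fewer predictors can enter the model.

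### With 40% drop-out, 75 enrolled patients leave 45, not the 54 required, so power is about 84% rather than the stated 90%

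*Protocol article*

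**What the plan says.** The whole sample size argument is one paragraph, section 3.2.2 of the protocol article. It takes FMA-UE as the outcome and assumes that "UL function improves with moderate standardized effect (Cohen’s *d* = 0.45), according to FMA-UE". The calculation is described as "Assuming an equivalent effect size *f* = 0.225, for repeated measures, within factors multivariate analysis of variance (MANOVA) design", "in one group with two measurements correlating 0.5", "given α = 0.05 and 1-β = 0.90". From these inputs it concludes that "a total recruitment of 54 consecutive subjects would be needed".

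The next sentence makes the allowance for losses: "Considering a drop-out rate of 40%, a final number of 75 patients will be considered sufficient to conclude the study". The Abstract (Methods/design) repeats the figure as the number to be included: "A total of 75 stroke patients". No formula is given for the step from 54 to 75.

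**The concern.** A drop-out rate is a fraction of the patients enrolled. To finish with n patients when a fraction d is lost, n/(1 − d) must be enrolled. Multiplying by (1 + d) instead always gives too few, and the gap widens as d grows. At 40% it is large: the factor is 1.67 by division and 1.40 by multiplication. The step from 54 to 75 is a factor of 1.39, which looks like the multiplication.

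If so, the required number, the drop-out rate and the enrolment figure cannot all be right, and the conclusion that 75 is enough fails on the article's own assumptions. This paragraph is the article's only justification of sample size. Unless corrected, it is likely to be carried into the results report.

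**Working it through.** **Inputs, all from section 3.2.2:** d = 0.45; f = 0.225 (= d/2); one group; m = 2 measurements; correlation ρ = 0.5; α = 0.05; target power 0.90; required n = 54; drop-out 40%; final number 75.

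**Step 1: reproduce the 54.** For a within-subject effect with two measurements, the test statistic is a noncentral F with 1 and n − 1 degrees of freedom and noncentrality

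λ = n·m·f²/(1 − ρ) = n × 2 × 0.050625/0.5 = 0.2025·n.

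Because 0.2025 = 0.45², this is the same as a two-sided paired t test with a standardised change of 0.45.

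| n with T0 and T1 | λ | Power |
|---|---|---|
| 45 | 9.11 | 0.839 |
| 53 | 10.73 | 0.895 |
| 54 | 10.94 | 0.901 |

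The smallest n that reaches 0.90 is 54. The stated figure is reproduced exactly, and none of its inputs includes an allowance for losses. It is therefore the number of patients needed with both assessments.

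**Step 2: apply the stated drop-out to the stated enrolment.** 75 × (1 − 0.40) = 45 patients, and 54 − 45 = 9 too few. From the table, power is 0.839 and the type II error is 1 − 0.839 = 0.161, against 0.10 planned.

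**Step 3: what would be consistent.**

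- Enrolment needed at 40% drop-out: 54/(1 − 0.40) = 90.
- Largest drop-out at which 75 still yields 54: 1 − 54/75 = 0.28.

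| Drop-out | Enrolment needed to keep 54 |
|---|---|
| 25% | 72 |
| 28% | 75 |
| 30% | 78 (77.1 rounded up) |
| 40% | 90 |

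**Step 4: where 75 may have come from.** 54 × 1.40 = 75.6, which gives 75 when truncated. This is the likely source but remains an inference.

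**The case against.** Five points can be made on the other side.

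*The cause is not documented.* Sample sizes are normally rounded up, so 54 × 1.4 would give 76. Meanwhile 75 is exactly 54/0.72, a correct division with 28% drop-out, so the rate itself may have been misstated. This is fair, and the article cannot settle it. It affects only the explanation: 75 × 0.60 is less than 54 whichever slip occurred.

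*The 75 may be completers, or the 54 may already include losses.* Neither reading works. The 75 appears only once drop-out is considered, and the Abstract gives it as the number to be included. The 54 is exactly what the inputs yield without losses.

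*A one-sided test would rescue the power.* At n = 45 a one-sided test has power of about 0.908. But a one-sided calculation needs only 44 patients, which contradicts the stated 54.

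*Imputation keeps the lost patients in the analysis.* Section 3.5 announces an intention-to-treat basis and multivariate imputation where much is missing. The sizing takes no credit for this, and imputing a missing T1 score restores little information about the pre-post change. The objection does justify describing the 45 precisely as patients with observed T1 data.

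*The effect is small and off the main aim.* This largely stands. Power of 84% is respectable, and 90% holds if drop-out stays at or below 28%. The overarching objective in section 2 is prediction, and the calculation covers only a one-group pre-post change. That limits the weight of the point, although nine fewer completers would also reduce the data available for the prediction model.

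**Conclusion.** The point holds. The requirement of 54, the 40% drop-out rate and the enrolment of 75 are mutually inconsistent, and nothing elsewhere in the article reconciles them. Under the stated assumptions, 75 enrolled gives 45 patients with both assessments and power of 0.839, about 6 percentage points below the claim.

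This rests on the article's own effect size and correlation, the two-sided test that reproduces its 54, and power counted on patients observed at both T0 and T1. It does not rest on how 75 was obtained. The statement needs correction because it is numerically false as written; the error does not in itself threaten the validity of the study.

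**What to change.** Rewrite the last sentence of section 3.2.2 so that its numbers agree, and show the formula n/(1 − drop-out). There are three consistent versions:

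1. Keep 75 and 40%: state that 45 patients with both assessments are expected and that power is about 84%.
2. Keep 75 and 90%: state that this tolerates drop-out of up to 28%, and say why that rate is realistic.
3. Keep 40% and 90%: enrol 90.

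The first two cost one paragraph of wording and a slightly less favourable statement of power or of tolerated loss, with no extra patients. The third needs 15 more patients (90 − 75) and a matching change to the total in the Abstract. Whichever is chosen, the text should make clear that 54 counts patients with FMA-UE at both T0 and T1, and that the power statement concerns the pre-post change only.
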